### Groups 4 health

Groups 4 Health (G4H) was developed to fill this void as a theory-driven, group psychotherapy intervention that targets loneliness [21, 22]. G4H is informed by the Social Identity Approach to Health (see [23, 24] for a summary), which is a conceptual framework that articulates how social group memberships, and the social identities associated with them, affect health and wellbeing.

To date, two trials of G4H have been completed. The first was a Phase I pilot [25], in which the program was delivered to 81 people (*M*_age_ = 20.95; *SD* = 5.05) presenting with loneliness and affective disturbance (symptoms of depression or anxiety), of whom 54 completed G4H, and 26 completed the 6-month follow up. This group was compared to a matched, but not randomised, assessment-only control group. G4H was found to significantly improve mental health (depression, general anxiety, social anxiety, and stress), well-being (self-esteem, life satisfaction) and social connectedness (loneliness, social functioning), both on program completion and at 6-month follow up. Moreover, G4H recipients had significantly better outcomes than those in the control group at the 6-month follow up on measures of depression, anxiety, stress and self-esteem. In line with the theorised mechanisms of the G4H intervention, analyses also showed that participants whose identification with their G4H group and their subjective sense of belonging to multiple groups increased were most likely to experience improvements in depression, anxiety, stress, loneliness, and life satisfaction.

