### Participants

Participants will be 200 young people presenting with psychological distress recruited from two sources in South East Queensland, Australia: (1) a community youth mental health service (headspace, five sites), and (2) a university psychology clinic (University of Queensland). The following criteria will be used in recruitment:

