#### Incentives

Participants will not be offered incentives to undertake the intervention, other than receipt of free, evidence-based mental health care. Those participants who are also students enrolled in first-year psychology courses will receive course credit for their participation in the program. To improve attendance at Module 5, where post-program assessments are conducted, all participants will be offered either a coffee or supermarket voucher (AUD$15 value) for attendance. To minimise attrition, participants will be offered AUD$50 incentive to complete each of the 6-month and 12-month follow up assessments. Participants will be followed up unless they actively withdraw from the trial (i.e., data will be sought from participants who did not attend group sessions or who no longer meet inclusion criteria, in order to honour the intention-to-treat principle).

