### Sample size power calculations

The CARR sample size was determined by power calculations for a non-inferiority trial, using effect sizes and retention rates from our published pilot study. We have estimated the non-inferiority margin based on historical evidence for the effect size of the active comparator (based on recommendations by [46] and [47]). The effect size of this CBT program versus control was *d* = 0.49 at 6 month follow up (recalculated from [28] using methods recommended by [19]). This corresponds to 2.2 points on the DASS-21 depression subscale (using the expected standard deviation for an adolescent population of 4.53; [31]). To have 0.80 power to detect this difference with an alpha level of 0.05*,* 67 people per condition would need to be retained at follow up. Assuming 50% eligibility and 67% survival rates, which are consistent with our pilot data, we anticipate that screening 400 people for eligibility (see Fig. 2) will lead to retention of *N* = 67 per condition at follow up [48]. However, this is a conservative estimate of retention due to the addition of incentives for follow up data completion in this trial [49].

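### The 67% retention assumed at follow-up matches the pilot's program completion; the pilot's 6-month retention was 32%, so the pilot supports 67 per arm and 0.80 power only at program completion

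*Protocol article*

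**What the plan says.** All references are to the protocol article.

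- *Sample size power calculations* says that the size was set "using effect sizes and retention rates from our published pilot study". It takes d = 0.49 for this CBT program against control at 6 months, converts it to 2.2 DASS-21 depression points with an SD of 4.53, and requires 67 per condition retained at follow-up for 0.80 power at alpha 0.05.
- The same section gets there by "Assuming 50% eligibility and 67% survival rates, which are consistent with our pilot data", starting from "screening 400 people for eligibility". It then adds that "this is a conservative estimate of retention due to the addition of incentives for follow up data completion in this trial".
- *Groups 4 health* (Background) describes the Phase I pilot, "in which the program was delivered to 81 people", "of whom 54 completed G4H, and 26 completed the 6-month follow up".
- *Participants* fixes the randomised number: "Participants will be 200 young people presenting with psychological distress".
- *Aims* sets H2, the non-inferiority hypothesis on depression, at program completion.
- *Incentives* pays AUD$50 for each of the 6- and 12-month assessments, and says that data will also be sought from people who did not attend sessions.

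**The concern.** The retention rate is said to come from the pilot and is applied to follow-up, but the pilot's follow-up retention, as reported in the same article, is less than half of it.

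Three things show that the section means the later assessments and not the end of treatment. Its effect size is a 6-month one. The incentives that it cites are paid only at 6 and 12 months. Table 1 labels T5 as post-treatment and keeps the term follow-up for T6 and T7.

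At stake is what a reader believes about the between-arm comparisons at 6 and 12 months. The abstract expects the benefit of G4H to be clearest at 12 months. The reader is told that retention there has been set cautiously, while the article's only pilot figure for a follow-up assessment points the other way.

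**Working it through.** **Inputs.** Margin 2.2 points, SD 4.53, power 0.80, alpha 0.05, 400 screened, 50% eligible, 67% retained (*Sample size power calculations*); 200 randomised (*Participants*) at 1:1 (*Trial design*); pilot counts 81, 54 and 26 (*Groups 4 health*). Sidedness is not stated. Two-sided 0.05 (equivalently one-sided 0.025) is used here because it reproduces the stated number; one-sided 0.05 gives 53 per arm and does not.

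**1. The plan's own figure.** n per arm = 2 × (1.96 + 0.842)² × (4.53 / 2.2)² = 2 × 7.85 × 4.24 = 66.6, rounded up to 67. Power at n = 67 is 0.803. The recruitment chain also holds: 400 × 0.50 × 0.67 / 2 = 67. The arithmetic is correct; the question is the retention input.

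**2. The pilot's rates.**
- Program completion: 54 / 81 = 66.7% (Wilson 95% interval 56% to 76%).
- 6-month follow-up, of all who received the program: 26 / 81 = 32.1% (Wilson 95% interval 23% to 43%).
- 6-month follow-up relative to program completers: 26 / 54 = 48.1%.

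The assumed 67% agrees with the first rate to the rounding and lies well above the interval for the second.

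**3. Between-arm power at other retention rates.** With 100 randomised per arm and n = 100 × retention, power = Φ[(2.2 / 4.53) × √(n / 2) − 1.96]:

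| Retained | n per arm | Power |
|---|---|---|
| 67% | 67 | 0.80 |
| 50% | 50 | 0.68 |
| 48% (26/54) | 48 | 0.66 |
| 32% (26/81) | 32 | 0.49 |

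For example, at n = 32: 0.4857 × 4 − 1.96 = −0.017, and Φ(−0.017) = 0.49. These values count completers only and ignore clustering by therapy group, which is a separate matter.

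**4. What a mixed model could recover.** This is an illustration with assumed values. Take 67 per arm observed at T5, 32 of them also at T6, and a T5–T6 correlation ρ of 0.5 or 0.7. The variance of an arm's T6 mean is proportional to (1 − ρ²) / 32 + ρ² / 67.
- ρ = 0.5: 0.75 / 32 + 0.25 / 67 = 0.0272, an effective n of about 37 and power of about 0.55.
- ρ = 0.7: 0.51 / 32 + 0.49 / 67 = 0.0232, an effective n of about 43 and power of about 0.61.

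The gain is real but modest.

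**5. What the word conservative would require.** Retention at 6 months would have to exceed 67%. Merely to reach it, the incentives would have to raise the pilot's rate by a factor of 67 / 32.1 = 2.1. The article gives no figure for their effect.

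**The case against.** Most of the case on the other side is sound, and it limits the point.

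- **H2 is set at program completion.** There 67% fits the pilot and 67 per arm reproduces. A reader might infer that the non-inferiority test is underpowered by this error; the documents do not support that. This stands.
- **H3 is a different test.** A reader might take 0.49 as the power for H3. *Analyses* defines H3 as no significant rise in depression and loneliness between T6 and T7 within the G4H arm. A two-sample power says nothing about a within-arm change, and the section fixes no between-arm criterion at T6 or T7. This stands.
- **32% is not a forecast.** CARR adds payments and pursues non-attenders; the article does not say whether the pilot pursued its non-completers. The planned model also uses all available timepoints. This stands, although the per-protocol set, which requires baseline and follow-up data, gains less from the model.
- **The origin of 67% is inferred.** The section does not say that it is program completion, and the source cited there is not at hand. This stands, but whatever its origin, 67% disagrees with the pilot's reported 6-month rate.
- **The exact fit of 400 × 0.50 × 0.67 = 134 proves nothing.** A reader might see in it a lack of reserve. It shows only that the number was sized to the assumption; whether 67% is cautious depends on the retention to be expected.
- **The Module 5 voucher.** A reader might infer from "To improve attendance at Module 5, where post-program assessments are conducted" that T5 data will be obtained only from attenders. *Incentives* also commits to seeking data from non-attenders, and *Randomisation* and *Measures* provide for online assessment. Whom to pay is a design preference and no part of this point.

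None of this supplies a figure that lifts 32% to 67%, or supports calling 67% conservative at follow-up.

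**Conclusion.** The point holds as an error in a stated input. As a follow-up rate, 67% is not consistent with the pilot as the article reports it (32.1% at 6 months), and the description as conservative is unsupported. The pilot backs 67 per arm and 0.80 power at T5 only.

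For between-arm comparisons at T6 and T7, the range from the pilot's 6-month rate to the assumed rate is 32% to 67% retained, or power of about 0.49 to 0.80. This rests on 100 randomised per arm, a difference of 2.2 points with SD 4.53 (d about 0.49), two-sided 0.05, completers only and no clustering. The lower end is an illustration that incentives, follow-up of non-attenders and the mixed model may improve on. The pilot reports no 12-month rate, so applying the same range to T7 is an assumption. The result leaves H2 at T5 untouched and gives no power for H3.

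**What to change.** In *Sample size power calculations*:

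1. State that 67% retention and 67 per condition refer to the T5 test of H2, and that 67% corresponds to program completion in the pilot (54 of 81), if the authors confirm that origin.
2. Report the pilot's 6-month retention beside it: 26 of 81, or 32%.
3. Delete the word conservative. The incentives can be named as a reason to expect better than the pilot, without a claim about how much better.
4. For between-arm comparisons at T6 and T7, give the range: about 0.49 at 32% retained, 0.68 at 50% and 0.80 at 67%. Label these as completer-based and before clustering, note that incentives, follow-up of non-attenders and the mixed model may raise the lower end, and do not attach them to H3.

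The cost is a few sentences of text. No extra participants, assessments or payments are needed.

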**Fig. 2 Fig2:**
[figure not shown]
Flow of participants in the CARR trial

### Analyses

Data quality will be improved by using a web interface that prompts (but does not force) participants to complete missing items. This will reduce missing data and prevent errors from manual data entry. Data quality will be checked by assessing ranges for each variable and interrogating outliers. We will examine the differences in baseline characteristics between the groups descriptively. Since differences between randomised groups at baseline could have occurred by chance, no formal significance testing will be conducted (in accordance with recommendations by [50]). No covariates will be included in the primary analysis (in accordance with recommendations by [51]). However, we will include exploratory analyses which assess the interaction between condition and baseline characteristics where indicated.

To assess the effect of intervention, group differences on the primary and secondary outcome measures, with all available timepoints included in the model, will be examined using a series of mixed effects repeated measures (MMRM) models, which will specify timepoint, participant, and therapy group as levels in the analyses. MMRM is a full information maximisation likelihood estimation strategy that can model data even when some observations are missing, and thus honours the intention-to-treat principle [52]. For all hypothesis testing, both intention-to-treat analyses (ITT; where all available data are included in MMRM) and per protocol analyses (PP; only including participants who met eligibility criteria throughout the trial period, were randomly assigned, completed the intervention according to the protocol, and had both baseline and follow up data) will be completed. Best fit, as determined by Information Criteria (e.g. AIC; BIC) method will be used for determining the covariance structure for MMRM models.

H1 will be considered supported if there is evidence of significant improvements in loneliness in the G4H condition (H1a), and a significant condition by time interaction, such that improvements in loneliness over time will be greater for the G4H condition than in the CBT condition (H1b). H2 will be considered supported if there is evidence of significant improvements in depression in both conditions, with a non-significant condition by time interaction. The non-inferiority margin will be a DASS-21 depression change score difference of 2.20. H3 will be considered supported if there is no significant increase in depression and loneliness scores between T6 and T7 in the G4H condition.

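### As conventionally fitted, the primary model compares raw change scores; constraining the T0 means to be equal across arms would be more precise and needs no new data

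*Protocol article*

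**What the plan says.** All of the following is in the protocol article.

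- **Covariates (Analyses).** "No covariates will be included in the primary analysis". The article supports this with a cited recommendation. Baseline characteristics enter only through exploratory interactions with condition.
- **Model (Analyses).** The mixed models are fitted "with all available timepoints included in the model", "which will specify timepoint, participant, and therapy group as levels in the analyses". DASS-21 depression is measured at T0 to T7, the UCLA-20 at T0, T5, T6 and T7 (Measures, Primary outcomes). T0 is thus one of the responses.
- **Tests (Analyses).** H1 needs improvement within G4H and "a significant condition by time interaction, such that improvements in loneliness over time will be greater for the G4H condition" than for CBT. H2 needs "significant improvements in depression in both conditions, with a non-significant condition by time interaction".
- **Margin (Analyses).** "The non-inferiority margin will be a DASS-21 depression change score difference of 2.20".
- **Sizing (Sample size power calculations).** Of d = 0.49 the article says "This corresponds to 2.2 points on the DASS-21 depression subscale", "using the expected standard deviation for an adolescent population of 4.53". It asks for 67 retained per condition, for 0.80 power at alpha 0.05.

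Nothing in the article equates the arms at T0 or adjusts for the T0 score.

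**The concern.** When T0 is a response with its own mean in each arm, the model treats the T0 difference between arms as an unknown to be estimated and subtracted. Randomisation already says that this difference is zero in expectation, and the Analyses section itself attributes baseline differences to chance. Estimating it adds noise to every contrast from T0.

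There is a second effect. A raw change score over-corrects for chance imbalance through regression to the mean. Groups of 5 to 9 people are allocated whole by simple randomisation (Randomisation, Intervention), so such imbalance is more likely than with individual allocation.

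What is at stake is the width of the confidence interval: for superiority on loneliness (H1), and for depression (H2) when the interval is set against the 2.20 margin.

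**Working it through.** **1. The plan's own figure.** 0.49 × 4.53 = 2.22, stated as 2.2. With two-sided alpha 0.05 (one-sided 0.025) and a true difference of zero:

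n per arm = 2 × (1.960 + 0.842)² × 4.53² / 2.2² = 66.6, so 67.

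This reproduces the article. One-sided 0.05 would give 53. Retention also agrees: 400 × 0.50 × 0.67 = 134, or 67 per arm.

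**2. Which SD this is.** 4.53 is a single-occasion SD. With equal SDs and baseline-to-follow-up correlation rho, the SD of change is 4.53 × √(2(1−rho)). It equals 4.53 only at rho = 0.5. The documents give neither rho nor an SD of change, so rho is an assumption below.

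**3. Change score against constrained baseline, complete unclustered data.** In units of 4.53², the outcome variance per person is 2(1−rho) for the change score and 1−rho² with a common T0 mean (or baseline adjustment). The variance ratio is (1−rho²)/(2(1−rho)) = (1+rho)/2, below 1 for every rho below 1.

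| rho | change: 2(1−rho) | constrained: 1−rho² | SE ratio | n per arm for 0.80 power | power at 67 per arm |
|---|---|---|---|---|---|
| 0.3 | 1.40 | 0.91 | 0.806 | 94 → 61 | 0.66 → 0.84 |
| 0.4 | 1.20 | 0.84 | 0.837 | 80 → 56 | 0.73 → 0.87 |
| 0.5 | 1.00 | 0.75 | 0.866 | 67 → 50 | 0.80 → 0.90 |
| 0.6 | 0.80 | 0.64 | 0.894 | 54 → 43 | 0.88 → 0.94 |
| 0.7 | 0.60 | 0.51 | 0.922 | 40 → 34 | 0.95 → 0.98 |

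At rho = 0.5 the 95% half-width at 67 per arm is 1.96 × 4.53 × √(2/67) = 1.53 points, and 1.53 × 0.866 = 1.33 with the constraint.

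**4. Eight timepoints, dropout and clustering.** Exact generalised least squares variances were computed for T0 to T7, with free or common T0 means and 14 groups of 7 per arm (98, near the planned 100). Correlation was constant or decayed with time. The therapy-group ICC was 0 or 0.05, with the group effect either present throughout or only after baseline. Either nobody or 33% were lost before T5.

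- Complete, unclustered: the T5 SE ratios were 0.806, 0.866 and 0.922 at rho 0.3, 0.5 and 0.7, exactly as in step 3.
- 33% loss and ICC 0.05, at T5: the ratios were 0.870-0.897, 0.913-0.930 and 0.948-0.959. The SE falls by about 10-13%, 7-9% and 4-5%. At rho = 0.5, for example, it falls from 0.733 to 0.681 or from 0.833 to 0.760, depending on the structure.
- The same at T7, if correlation decays with time: the SE falls by about 14-20%.

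The constrained model was more precise in every scenario.

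**5. Imbalance.** Without clustering and with equal SDs, each point of chance T0 difference shifts the expected raw change difference by (1−rho) points: 0.7, 0.5 or 0.3 at rho 0.3, 0.5 or 0.7.

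**The case against.** - **The planned analysis is sound.** A reader might infer from the remarks on imbalance that the plan is biased. It is not: under randomisation the change-score contrast is unbiased. The imbalance concerns the sample that happens to be drawn. The fault is lost precision only.
- **Free T0 means are not stated.** True. They are the conventional reading of a condition-by-time model, and an analysis plan could specify otherwise. A T0 constraint adds no covariate, so it even fits the no-covariate rule. But the article fixes T0 as a response, a bar on covariates and a change-score margin, and together these lead to the change-score comparison unless a constraint is written in. The recommendation cited against covariates cannot be checked here.
- **A narrower interval does not help H2 as worded.** This stands. H2 is supported by a non-significant interaction, and under that rule more precision makes any true non-zero difference more likely to defeat H2. The gain for H2 exists only when the interval is compared with the margin.
- **The size rests on an assumed rho.** This also stands. The 13% at rho = 0.5 needs complete, unclustered data, while the plan expects 67% retention and models therapy group.
- **Baseline as a covariate is not a free substitute.** One might think that it could simply be added, with T1 to T7 as outcomes. That would break the stated tests. An effect constant after baseline would move into the condition main effect, within-arm improvement from T0 would have no T0 response, and the UCLA-20 has no T1 to T4 scores.

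**Conclusion.** The point holds as one of efficiency. As conventionally fitted, the primary model discards information that the trial already collects, and the direction is the same for every rho below 1. A realistic size at T5, with the planned loss and an assumed ICC of 0.05, is a standard error smaller by 7-9% at rho = 0.5. That is worth about 16-21% more participants (1/0.93² = 1.16; 1/0.91² = 1.21). At rho = 0.3 the reduction is 10-13%; at rho = 0.7 it is a modest 4-5%.

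A reader might also infer that the change-score analysis leaves the trial short of its 0.80 power. The documents do not show this. Before clustering, power at 67 per arm falls short if rho is below 0.5 but reaches 0.88 at 0.6 and 0.95 at 0.7, and rho is not given.

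Two limits apply. The interaction for DASS-21 depression spans up to eight timepoints, so the argument applies to each contrast from T0 within it. With missing data, the equality with raw change is approximate.

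**What to change.** In Analyses, replace the no-covariates sentence with: *The primary model constrains the T0 mean to be equal in both arms; no other covariates are included.* T0 stays a response. In practice the condition main effect is left out, and condition-by-time terms are kept for each timepoint after T0. The interaction test, the within-arm improvement tests, the estimand and the margin scale are unchanged.

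If baseline is used as a covariate instead, the test must be restated as the adjusted arm difference at T5 (and T6, T7), using only the timepoints at which each scale is measured.

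The cost is one sentence and no new data. The one condition is that each participant completes T0 before the group's allocation is known, because participants and research staff are unblinded. Recruitment places baseline measures at screening, and Randomisation allocates a group only after it has been recruited, which fits. Measures says only that T0 precedes the intervention, so the order should be stated outright. For H2, the benefit also requires that the confidence interval be compared with 2.20.

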### Aims

The project aims to evaluate G4H in comparison to the current gold standard evidence-based psychological treatment for youth depression, CBT. Based on the existing evidence, we predict:*Hypothesis 1:* At program completion, G4H will be superior to CBT in reducing loneliness (a major risk factor for relapse in depression).*Hypothesis 2:* At program completion, G4H will be as effective as CBT in reducing symptoms of depression (i.e., be non-inferior)*Hypothesis 3:* The benefits of G4H for loneliness and depression will be sustained at 12-month follow up.

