### Measures

Each participant will be asked to complete online surveys (or paper-and-pencil if they prefer) at eight time points. The full questionnaire package measuring all outcomes of interest will be administered before the intervention (T0), on its completion (T5), 6 months later (T6) and 12 months later (T7) – see Table 1 for a summary. These should take about 10–20 min on each occasion. In addition, a brief one-page questionnaire will be administered at the end of each session (T1, T2, T3, and T4), which will (only) include measures of depression symptoms, loneliness, module feedback, and group identification.

**Table 1 Tab1:** Overview of CARR measures and timepoints of measurement

Construct	Measure	T0 Baseline	T1 After session 1	T2 After session 2	T3 After session 3	T4 After session 4	T5 Post-treatment	T6 6-month follow up	T7 12-month follow up
Primary outcomes	Depression (DASS-21)	•	•	•	•	•	•	•	•
	Depression (PHQ-9)	•					•	•	•
	Loneliness (4 item)	•	•	•	•	•	•	•	•
	Loneliness (20 item)	•					•	•	•
Secondary outcomes	Social anxiety	•					•	•	•
	GP attendance (last month)	•					•	•	•
	Wellbeing	•					•	•	•
	Life satisfaction	•					•	•	•
	Self esteem	•					•	•	•
	Subjective physical health	•					•	•	•
Process measures	Multiple group membership	•					•	•	•
	Multiple group compatibility	•					•	•	•
	Mental illness identity	•					•	•	•
	Group cohesion						•		
	Therapy group identification		•	•	•	•	•		
	Service identification						•		
Acceptability/feasibility	Useful		•	•	•	•	•	•	•
	Enjoyed						•	•	•
	Interesting						•	•	•
	Learnt something						•	•	•
	Homework completion		•	•	•	•	•		
	Facilitator questionnaire		•	•	•	•	•		
	Attendance		•	•	•	•	•		

Notes: *DASS21* Depression Anxiety Stress Scales (21 item)

*PHQ-9* Patient Health Questionnaire (9 item).

*GP* General Practitioner

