### Primary outcomes

*Depression, Anxiety and Stress Scale* [30]*.* This measure comprises 21 items, 7 for each construct, for example “I felt that life was meaningless”, rated on a 4-point scale (0 = did not apply to me at all, 3 = applied to me very much, or most of the time. It has been validated for use with adolescents as young as 11 years in Australia [31], with an improvement greater than 3 points considered clinically significant [32]. The full DASS-21 (including anxiety and stress subscales) will be administered at T0, T5, T6 and T7, while the depression subscale will be administered at all timepoints T0-T7. The 9-item Patient Health Questionnaire is included as an additional measure of depression (T0, T5, T6, T7); this will be used as a screening tool rather than as the primary outcome measure.

*UCLA-20:* The UCLA Loneliness scale has been validated for use with a young adult sample [33, 34]. It comprises 20 items, for example “Felt isolated from others” requiring a response on a 4-point scale (1 = never, 4 = often). The full scale will be included at T0, T5, T6 and T7, and a 4-item version of the UCLA scale will be included in the end of session questionnaire (T1-T4).

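### H1 and H2 are stated at program completion, but the decision rules name no timepoint and can be read as an interaction over all visits to 12 months

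*Protocol article*

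**What the plan says.** In the protocol article, the Aims date the first two hypotheses. H1 reads "At program completion, G4H will be superior to CBT in reducing loneliness". H2 reads "At program completion, G4H will be as effective as CBT in reducing symptoms of depression (i.e., be non-inferior". The 12-month visit has its own hypothesis, H3: "The benefits of G4H for loneliness and depression will be sustained at 12-month follow up".

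The Analyses section examines "group differences on the primary and secondary outcome measures, with all available timepoints included in the model". The rule for H1 then has two parts. H1a needs improvement in loneliness within G4H. H1b asks for "a significant condition by time interaction, such that improvements in loneliness over time will be greater for the G4H condition than in the CBT condition". The rule for H2 needs improvement in depression in both arms and a non-significant condition-by-time interaction. The margin is a difference of 2.20 in DASS-21 depression change. None of these statements names a visit.

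Table 1 in Measures gives the visits. DASS-21 depression has eight (T0 to T7) and the 20-item loneliness scale has four (T0, T5, T6, T7). Under primary outcomes the table also lists "Depression (PHQ-9") and a 4-item loneliness scale marked at all eight visits. The Primary outcomes text says of the PHQ-9 that "this will be used as a screening tool rather than as the primary outcome measure", and places the 4-item scale in the end-of-session questionnaire at T1 to T4.

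**The concern.** A condition-by-time interaction over all visits asks whether the arms' profiles differ anywhere between baseline and 12 months. H1 and H2 ask whether the arms differ in change from baseline to T5. The two answers can diverge, and the plan's own expectation is a pattern in which they would: the Abstract (Methods) expects the benefit of G4H to show most clearly at 12 months.

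At stake is what a positive or negative result means. If the arms separate only after T5, H1 could be reported as supported at program completion with no difference there. If G4H falls behind only after T5, H2 could be reported as failed although the arms were equal at program completion. A test with 3 or 7 degrees of freedom also yields no single estimate to set against 2.20.

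**Working it through.** **The plan's own figure.** Inputs from Sample size power calculations: difference 2.2, SD 4.53, power 0.80, alpha 0.05. n per arm = 2 × (1.960 + 0.842)² × 4.53² / 2.2² = 15.70 × 4.240 = 66.6, so 67. Retention: 400 × 0.50 × 0.67 / 2 = 67. The stated 67 per condition reproduces, so the sample size arithmetic is not in question.

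**Comparing the two tests.** Assumptions that are not in the document: 67 per arm at every visit, compound symmetry with within-person correlation ρ of 0.3, 0.5 or 0.7, no clustering by therapy group, and differences δ in SD units. The size 0.49 is borrowed from the sample size section, where it is CBT versus control on depression at 6 months. It is not an estimate for G4H versus CBT on loneliness, so 0.3 is shown as well.

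The all-visit interaction (number of visits minus 1 df, 5% level) has noncentrality λ = n × Σ(δ − mean δ)² / [2(1 − ρ)], summed over all visits including baseline.

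*H1, UCLA-20, four visits, δ = (0, 0, d, d).* The sum of squares is d², so λ = 67d² / [2(1 − ρ)].

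| Late difference d | ρ = 0.3 | ρ = 0.5 | ρ = 0.7 |
|---|---|---|---|
| 0.49: λ | 11.49 | 16.09 | 26.81 |
| 0.49: P(significant), 3 df | 0.82 | 0.94 | >0.99 |
| 0.30: λ | 4.31 | 6.03 | 10.05 |
| 0.30: P(significant), 3 df | 0.38 | 0.52 | 0.76 |
| T5 contrast, two-sided | 0.05 | 0.05 | 0.05 |

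These use the chi-square reference. An F reference with 132 denominator df lowers them by about one point or less (0.81, 0.93, 0.99 and 0.37, 0.51, 0.75). In the direction favouring G4H, the T5 contrast is significant in 2.5%.

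*H2, DASS-21 depression, eight visits, d = 2.2/4.53 = 0.486.*

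- Arms equal through T5, G4H worse by 2.2 points at T6 and T7: the sum of squares is 2d² − (2d)²/8 = 1.5d², so λ = 16.93, 23.70, 39.51. The 7-df interaction is significant, so H2 fails, with probability 0.87, 0.97, >0.99.
- G4H worse by 2.2 points at T5 only: the sum of squares is 0.875d², so λ = 9.88, 13.83, 23.05. The interaction is non-significant with probability 0.39, 0.22, 0.04, so that part of the H2 rule would be met despite a true deficit equal to the margin.

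**Is it a power problem?** Not mainly. With a 0.49 SD difference in UCLA-20 at T5 only, the 3-df interaction has power 0.69, 0.84, 0.98, against 0.67, 0.81, 0.96 for the T5 contrast. The problem is which visits can produce the result.

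**The case against.** The strongest reply is that the article never calls the test overall, joint or multi-degree-of-freedom. A T0-to-T5 contrast from an all-visit model is itself a condition-by-time term, and the choice of contrast is often left to an analysis plan, which is not shown here. This stands in part: a reader may infer that the protocol prescribes an omnibus test, and it does not say so. But the article does fix the timepoint of its hypotheses and does state their decision rules, and the rules omit the timepoint. That is a mismatch between two stated parts of the same document.

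It is also fair that including every visit is sound modelling and serves the Abstract's aim of comparing the arms at completion, 6 and 12 months. H1 further requires improvement within G4H and a direction favouring G4H, so a difference at some visit is not enough by itself. A late G4H advantage would still satisfy the direction.

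Two stronger readings are tempting. One is that two loneliness scales give H1 two chances of success. No passage says that either scale may decide H1. The Primary outcomes text headlines the UCLA-20 and places the 4-item version at T1 to T4, so on that text the UCLA-20 is the loneliness measure at program completion. The other is that the depression outcome is unsettled because Table 1 lists the PHQ-9 as primary. The text resolves this by making the PHQ-9 a screening tool, and the margin is set on the DASS-21. What remains in both cases is a disagreement between table and text.

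The size of the effect is a chosen scenario. It needs no difference at T5 and a clear one later, and it ignores the therapy-group level that the analysis model includes.

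**Conclusion.** The point holds as a mismatch: H1 and H2 are dated at T5, while their decision rules and the 2.20 margin carry no date and draw on a model that runs to 12 months. If the interaction is taken over all visits, a late-only UCLA-20 difference would make it significant in about 82% to over 99% of trials at 0.49 SD, and 38% to 76% at 0.3 SD, against 5% for the T5 contrast. These figures rest on the assumed correlations, compound symmetry, no clustering and an assumed late difference. The percentages move with those choices, but the possibility of a result driven by T6 or T7 does not go away. The documents do not support saying that an omnibus test is prescribed, that H1 has two routes to success, or that all visits should not be in the model. The matter should be corrected, and it needs no redesign.

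**What to change.** Keep the all-timepoint model. In Analyses, state that:

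- H1b is tested by the G4H minus CBT contrast in UCLA-20 change from T0 to T5.
- H2 is judged on the same T0-to-T5 contrast in DASS-21 depression change, with its confidence limit compared with 2.20.
- T6 and T7 between-arm contrasts are reported as follow-up results. H3 stays as written.

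As a minor alignment, make Table 1 agree with the Primary outcomes text: PHQ-9 as a screening tool, 4-item loneliness as an end-of-session measure.

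The cost is wording and a table edit, with the same data and model. One part goes further than naming a visit: comparing a confidence limit with the margin replaces the non-significance criterion for H2. That is a change of decision rule and should be recorded as one.
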